## Abstract

**Background:**

Schizophrenia (SCZ) is characterized by cognitive deficits that are linked to prefrontal cortex dysfunction. While transcranial direct current stimulation (tDCS) shows promise for improving cognition, the effects of intensified 3mA tDCS protocols on brain physiology are unknown. This project aims to elucidate the neurophysiological and cognitive effects of an intensified prefrontal tDCS protocol in SCZ.

**Methods:**

The study is designed as a randomized, double-blind, 2-arm parallel-group, sham-controlled, trial. Forty-eight participants with SCZ and cognitive impairment (measured via a set of executive functions tests) will be randomly allocated to receive either a single session of active (n = 24) or sham (n = 24) tDCS (20-min, 3-mA). The anodal and cathodal electrodes are positioned over the left and right DLPFC respectively. The stimulation occurs concurrently with the working memory task, which is initiated precisely 5 minutes after the onset of tDCS. Structural and resting-state (rs-fMRI) scans are conducted immediately before and after both active and sham tDCS using a 3 Tesla scanner (Siemens Prisma model) equipped with a 64-channel head coil. The primary outcome will be changes in brain activation (measures vis BOLD response) and working memory performance (accuracy, reaction time).

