While non-invasive brain stimulation techniques are safe methods for directly modifying brain functions in humans and studying the causality of brain-behavior relationships [17], neuroimaging methods, including functional magnetic resonance imaging (fMRI), enable the study of brain function in vivo. Combining these methods allows for experimental induction of alterations in neural processes that have impacts on cognition and underlying physiological processes, as well as assessing cognitive brain correlations [17, 18]. the cognitive benefits of tDCS in SCZ partly rely on the dosage of stimulation [4, 19], which is also observed in healthy populations [20]. Recent physiological findings suggest that an intensified protocol with anodal tDCS (3 mA) can induce longer-lasting and stronger aftereffects on motor cortex plasticity [21], which is also transferred to the prefrontal cortex [22]. Furthermore, for the cognitive effects of stimulation, it is important to consider its effects on functional networks [23]. While previous studies have shown that tDCS can improve cognition in a dose-dependent manner in SCZ [19], the physiological mechanisms underlying these effects have not been fully elucidated. Given the importance of stimulation intensity for cognitive outcomes, it is relevant to evaluate the efficacy of an intensified 3mA tDCS protocol, which has not yet been studied in SCZ, to the best of our knowledge.

This study was designed to investigate the effects of online 3-mA prefrontal tDCS on working memory and the associated brain physiology in patients with SCZ. Specifically, the objectives of the present study were to examine (1) changes in working memory task performance during online 3-mA tDCS in SCZ, (2) changes in blood-oxygen-level-dependent (BOLD) response in the targeted regions after 3-mA tDCS, (3) changes in functional connectivity of executive control networks after 3-mA tDCS, and (4) associations between changes in performance and functional connectivity in patients with SCZ. We hypothesized that compared to sham, 3-mA prefrontal tDCS will improve working memory performance, increase frontal activation, and strengthen executive network connectivity. We also expect that those with greater improvements in connectivity will exhibit better performance. Investigating the neurophysiological effects of intensified tDCS can inform the optimization of tDCS protocols for SCZ.

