**Fig 1 pone.0306422.g001:**
[figure not shown]
SPIRIT schedule. Note: PANAS: Positive Scale, Negative Scale, and General Psychopathology Scale; ESQ: Executive Skills Questionnaire for Adults.

Eligible participants, after confirming inclusion criteria and obtaining informed consent, undergo comprehensive baseline assessments. These assessments include reconfirming the diagnosis using the Clinician-Rated Dimensions of Psychosis Symptom Severity [26], administered by a trained psychiatrist. Additionally, participants complete the native language versions of the Montreal Cognitive Assessment (MoCA-P) scale [27] and Executive Skills Questionnaire for Adults (ESQ) [28, 29], and their symptomatology is evaluated using the Positive Scale, Negative Scale, (PANSS) [30, 31]. The cognitive screening and clinical assessment will be conducted with native language versions of each scale with sufficient psychometric features. At least one week prior to participating in the intervention session (tDCS/fMRI), a baseline assessment of working memory is conducted using the n-back test. During the intervention session, participants are first checked for sleep pressure as it greatly impacts cortical excitability, tDCS-induced plasticity and cognitive performance [32]. Then, participants in the active group undergo online anodal tDCS at 3 mA for 20 minutes. The anodal electrode is positioned over the left DLPFC while the cathode is placed over the right DLPFC. This stimulation occurs concurrently with the working memory task, which is initiated precisely 5 minutes after the onset of tDCS. Brain stimulation is conducted in a room next to the scanner and structural and resting-state (rs-fMRI) scans are conducted immediately before and after both active and sham tDCS (Fig 2). To keep the time interval stable, we start the post-stimulation rs-fMRI 5 minutes after the end of stimulation to move the subject on the scanner bad and prepare it.

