### 2.9 Magnetic resonance imaging

MRI assessments will be performed using a Siemens MAGNETOM Prisma 3 Tesla scanner, equipped with a 64-channel head coil. These assessments will take place both before and immediately after the intervention. Each MRI session will encompass whole-brain structural images with T1-weighted acquisition and rs-fMRI scans. Each MRI session will include the acquisition of whole-brain structural images and resting-state fMRI (rs-fMRI) scans. The T1-weighted images will be acquired over five minutes using MPRAGE pulse sequences with parameters set at a TR of 1800 ms, TE of 3.53 ms, a voxel size of 1 × 1 × 1 mm^3^, and a flip angle of 7°. Additionally, rs-fMRI will be conducted for 15 minutes using an EPI sequence with a TR of 2000 ms, TE of 30 ms, a voxel size of 3 × 3 × 3 mm^3^, and a flip angle of 90°.

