### 2.12 Statistical methods

To assess the efficacy of the tDCS intervention, we will conduct a mixed model analysis of variance (mixed-ANOVA) on the n-back task indices, including d-prime, reaction time, and accuracy with time (before and after tDCS) as the within-subject factor and group (active tDCS and sham tDCS) as the between-group factor and their interaction. The group × time interaction effect and the main effect of group and time will be explored to see if changes in working memory performance and brain activation (two key dependent variables) are influenced by the type of stimulation (group factor) and time (before vs during stimulation). The normality and homogeneity of data distribution, and variance will be confirmed by Shapiro-Wilk and Levin tests, respectively. Mauchly’s test will also be used to evaluate the sphericity of the data before performing the ANOVA. In case the assumption of sphericity was violated, the degrees of freedom were corrected using Greenhouse-Geisser estimates of sphericity. To investigate the associations between changes in brain activity/connectivity and task performance changes, we will employ the Pearson correlation test. This test will help identify potential relationships between changes in brain activity and task performance, providing valuable insights into the neural mechanisms underlying our observations. All statistical analyses will be conducted using R [45].

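### Brain activation is named as a primary outcome and ANOVA variable, but the protocol acquires only resting-state scans and defines no activation measure

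*Protocol article*

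**What the plan says.** Activation appears in four roles:

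- **Primary outcome** (Abstract, Methods): "The primary outcome will be changes in brain activation (measures vis BOLD response) and working memory performance (accuracy, reaction time".
- **Objective 2** (section 1): "changes in blood-oxygen-level-dependent (BOLD) response in the targeted regions after 3-mA tDCS". Objective 3 is a separate item, on connectivity of executive control networks.
- **Hypothesis** (section 1): relative to sham, "3-mA prefrontal tDCS will improve working memory performance, increase frontal activation, and strengthen executive network connectivity".
- **Analysis variable** (section 2.12): the group-by-time model is to show whether "changes in working memory performance and brain activation (two key dependent variables) are influenced by the type of stimulation". The same sentence describes time as a comparison of the state before stimulation with the state during it.

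On data collection, section 2.1 says "Brain stimulation is conducted in a room next to the scanner and structural and resting-state (rs-fMRI) scans are conducted immediately before and after" active and sham tDCS. It has the n-back run while the current is on, starting 5 minutes after onset, and it starts the post-stimulation resting scan 5 minutes after the current stops. Section 2.9 states: "Each MRI session will encompass whole-brain structural images with T1-weighted acquisition and rs-fMRI scans".

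Section 2.10.2 lists two imaging primaries. Both are changes in resting-state functional connectivity: one between regions of interest, the other between the cortex under the electrodes and the whole brain. The imaging part of section 2.12 plans seed-based correlations and ICA.

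**The concern.** The parts of the article that state the claim and the parts that describe the data do not match. An activation result normally means a change in regional signal against a task or stimulus contrast. A functional-connectivity result is a correlation between time series, and it can rise or fall without showing whether activity in the frontal cortex went up.

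The Abstract and section 2.10.2 therefore name different imaging primary outcomes, and someone checking the eventual results paper against this article could not tell which was prespecified. Two bad outcomes are possible: a declared primary outcome is silently dropped, or a connectivity finding is reported as increased frontal activation. Because the term is undefined, it also leaves room to choose a measure after the data have been seen.

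**Working it through.** The point itself has no figure to reproduce. The check is to set the statements side by side and ask, for each use of activation, which data and which analysis would serve it.

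**1. Is BOLD signal recorded during the n-back?** Section 2.10.1 places the task at a baseline session and during online stimulation. Section 2.10.2 adds an assessment at 24 hours. Section 2.1 puts the baseline task at least one week before the tDCS/fMRI session and puts stimulation, with its concurrent task, in a room beside the scanner. Scanning is described only immediately before and after stimulation. No n-back assessment coincides with a scan, so there is no task-evoked response to estimate.

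**2. Is BOLD signal recorded during stimulation?** No. There is a scan before stimulation and one that starts 5 minutes after it ends. The pre-versus-during contrast that section 2.12 applies to activation has no second time point for any imaging variable, connectivity included. For the n-back the contrast does work, because the task is performed during stimulation.

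**3. Do the resting scans feed a defined activation measure?** Section 2.9 specifies a T1 sequence and a 15-minute resting EPI run. Section 2.10.2 defines connectivity outcomes only. Section 2.12 plans seed-based correlation and ICA only. No activation contrast and no regional resting-amplitude measure is defined in the article.

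**4. Could activation simply mean connectivity here?** The article separates the two three times: objective 2 against objective 3; frontal activation against network connectivity in the hypothesis; and cortical activation listed beside connectivity in section 3. If they are the same thing, objective 2 repeats objective 3. If they differ, objective 2 has no defined measure. The text needs changing either way.

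**5. What is affected?**

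| Item | Affected | Out of |
|---|---|---|
| Objectives (section 1) | 1 (objective 2) | 4 |
| Active-versus-sham directional hypotheses (section 1) | 1 (frontal activation) | 3 |
| Main dependent variables named for the ANOVA (section 2.12) | 1 (brain activation) | 2 |
| Imaging primaries (section 2.10.2) | 0 | 2 |

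The sample size in section 2.5 (minimum 42, raised to 48 for dropout) is derived from three measurements of working memory. It uses no imaging outcome, so this point does not change it.

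**The case against.** The best defence is that activation is loose wording. The section that formally lists outcomes, 2.10.2, is clear, and its two imaging primaries have both data (2.9) and an analysis (2.12). Section 2.12 elsewhere runs brain activity and connectivity together as if interchangeable, and it first describes the time factor for the n-back model as before and after tDCS. On that view the Abstract and the ANOVA paragraph mislabel outcomes that are properly defined elsewhere, and nothing listed in 2.10.2 would go unreported.

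Much of this stands. A reader might infer that the trial has no data for one of its primary outcomes, or that its imaging aim cannot be tested at all. The documents do not support either inference. The listed imaging primaries can be analysed as planned. The article never says that activation must be task-evoked, and a local measure of resting activity, such as the amplitude of low-frequency fluctuations, could be derived from the scans already being collected.

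The defence does not cover section 1, where activation and connectivity are separate objectives and separate hypotheses, so mislabelling cannot account for every use. It also leaves the pre-versus-during factor attached to activation in 2.12. Nor is this a detail that a fuller protocol or a SAP could be expected to supply: the article describes the scanning sessions explicitly, and the conflict is between its own statements.

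**Conclusion.** The contradiction holds, within limits. Task-evoked activation cannot be estimated from this design, no other activation measure is defined, and the pre-versus-during contrast cannot be computed for any imaging variable. The problem is confined to the activation outcome in the Abstract, objective 2, the frontal-activation hypothesis and the activation variable in section 2.12. Connectivity and working-memory outcomes are unaffected and remain testable.

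This is an internal inconsistency, not a failure of acquisition: no scan, visit or participant number has to change. It still needs correcting before results are analysed, because it concerns a declared primary outcome and because reporting connectivity as activation would be a substantive error. The conclusion assumes that sections 2.1 and 2.9 describe all the functional scanning in the trial. If task fMRI were in fact acquired, those two sections would be wrong instead.

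**What to change.** - **Abstract and section 2.12:** replace brain activation (BOLD response) with the two resting-state connectivity outcomes exactly as listed in 2.10.2. Do not bring in a new seed or network contrast at this step, since that would add a primary outcome when the aim is to reconcile wording.
- **Section 2.12, time factor:** for imaging variables, set time to before versus after stimulation. Changing the variable's name alone would leave a contrast that cannot be computed.
- **Objective 2 and the frontal-activation hypothesis:** either delete them, since objective 3 already covers connectivity, or restate them as a prespecified exploratory measure of resting local activity in the DLPFC (for example ALFF or fALFF) from the existing scans. Label it resting activity, not activation. Rewriting objective 2 as connectivity would largely duplicate objective 3.

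The cost is a documented wording change, plus a little extra image processing if the exploratory measure is kept. The price in substance is a narrower claim: the trial could report changes in resting connectivity, and perhaps resting activity, but not that stimulation increased frontal activation. Section 2.1 describes recruitment as under way, so on the article's account the change can be dated and recorded before the groups are compared.

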**Discussion:**

The results of this study are helpful in optimizing tDCS protocols in SCZ and inform us of neurocognitive mechanisms underlying 3 mA stimulation. This study will additionally provide initial safety and efficacy data on a 3 mA tDCS protocol to support larger clinical trials. Positive results could lead to rapid and broader testing of a promising tool for debilitating symptoms that affect the majority of patients with SCZ. The results will be made available through publications in peer-reviewed journals and presentations at national and international conferences.

## 1. Introduction

SCZ (SCZ) is one of the most severe neuropsychiatric disorders, with poor response or adherence to current treatment strategies in 40% of patients [1]. In the latest Global Burden of Disease Study, SCZ is among the top 20 diseases in 2021 in disability metrics [2]. Cognitive impairments, particularly in working memory and executive functions, are more pronounced than positive symptoms like hallucinations and delusions in SCZ [3–5]. These impairments are associated with significant functional impairment and poor prognosis. SCZ is characterized by frontal abnormalities, especially in the prefrontal cortex (PFC), which are linked to executive dysfunction and working memory deficits [5–7]. Consequently, interventions targeting cognitive control through PFC activity modulation have been suggested as a possible treatment for SCZ [4, 8] and other disorders with frontal problems [9–13]. Transcranial direct current stimulation (tDCS) is a safe and noninvasive brain stimulation technique for modulating brain excitability [14, 15] and has been increasingly applied in SCZ for cognitive benefits [8, 16]. Despite promising preliminary results in SCZ, the mechanisms underlying the observed effects and systematic evaluation of intervention protocols that can lead to clinically optimal effects have not been well explored.

While non-invasive brain stimulation techniques are safe methods for directly modifying brain functions in humans and studying the causality of brain-behavior relationships [17], neuroimaging methods, including functional magnetic resonance imaging (fMRI), enable the study of brain function in vivo. Combining these methods allows for experimental induction of alterations in neural processes that have impacts on cognition and underlying physiological processes, as well as assessing cognitive brain correlations [17, 18]. the cognitive benefits of tDCS in SCZ partly rely on the dosage of stimulation [4, 19], which is also observed in healthy populations [20]. Recent physiological findings suggest that an intensified protocol with anodal tDCS (3 mA) can induce longer-lasting and stronger aftereffects on motor cortex plasticity [21], which is also transferred to the prefrontal cortex [22]. Furthermore, for the cognitive effects of stimulation, it is important to consider its effects on functional networks [23]. While previous studies have shown that tDCS can improve cognition in a dose-dependent manner in SCZ [19], the physiological mechanisms underlying these effects have not been fully elucidated. Given the importance of stimulation intensity for cognitive outcomes, it is relevant to evaluate the efficacy of an intensified 3mA tDCS protocol, which has not yet been studied in SCZ, to the best of our knowledge.

This study was designed to investigate the effects of online 3-mA prefrontal tDCS on working memory and the associated brain physiology in patients with SCZ. Specifically, the objectives of the present study were to examine (1) changes in working memory task performance during online 3-mA tDCS in SCZ, (2) changes in blood-oxygen-level-dependent (BOLD) response in the targeted regions after 3-mA tDCS, (3) changes in functional connectivity of executive control networks after 3-mA tDCS, and (4) associations between changes in performance and functional connectivity in patients with SCZ. We hypothesized that compared to sham, 3-mA prefrontal tDCS will improve working memory performance, increase frontal activation, and strengthen executive network connectivity. We also expect that those with greater improvements in connectivity will exhibit better performance. Investigating the neurophysiological effects of intensified tDCS can inform the optimization of tDCS protocols for SCZ.

## 2. Methods and analysis

### 2.1 Trial design

The study design and schedule were reported in accordance with the SPIRIT guidelines [24] (Fig 1). In this study, we conducted a randomized, double-blind, parallel-group, sham-controlled investigation at the National Brain Mapping Laboratory and Institute for Research in Fundamental Sciences in Tehran, Iran, in collaboration with the Department of Psychiatry at the University of British Columbia in Canada and the Department of Psychology and Neurosciences at ifado, Germany. Our report adhered to the Consolidated Standards of Reporting Trials (CONSORT) statement for non-pharmacological treatments [25]. Currently, we are in the recruitment phase, aiming to enroll a cohort of 48 participants diagnosed with SCZ Spectrum and Other Psychotic Disorders, according to the DSM-5 criteria, by a licensed psychiatrist. These participants will fall within the age range of 18–50 years. To ensure the scientific rigor of our research, we will systematically and randomly allocate these participants into one of two parallel groups. Each group will receive either active or sham tDCS. Importantly, half of the participants will undergo a single tDCS session, which involves anodal and cathodal stimulation over the left and right Dorsolateral Prefrontal Cortex (DLPFC) respectively. The other half will receive sham stimulation as part of this research study.

**Fig 1 pone.0306422.g001:**
[figure not shown]
SPIRIT schedule. Note: PANAS: Positive Scale, Negative Scale, and General Psychopathology Scale; ESQ: Executive Skills Questionnaire for Adults.

Eligible participants, after confirming inclusion criteria and obtaining informed consent, undergo comprehensive baseline assessments. These assessments include reconfirming the diagnosis using the Clinician-Rated Dimensions of Psychosis Symptom Severity [26], administered by a trained psychiatrist. Additionally, participants complete the native language versions of the Montreal Cognitive Assessment (MoCA-P) scale [27] and Executive Skills Questionnaire for Adults (ESQ) [28, 29], and their symptomatology is evaluated using the Positive Scale, Negative Scale, (PANSS) [30, 31]. The cognitive screening and clinical assessment will be conducted with native language versions of each scale with sufficient psychometric features. At least one week prior to participating in the intervention session (tDCS/fMRI), a baseline assessment of working memory is conducted using the n-back test. During the intervention session, participants are first checked for sleep pressure as it greatly impacts cortical excitability, tDCS-induced plasticity and cognitive performance [32]. Then, participants in the active group undergo online anodal tDCS at 3 mA for 20 minutes. The anodal electrode is positioned over the left DLPFC while the cathode is placed over the right DLPFC. This stimulation occurs concurrently with the working memory task, which is initiated precisely 5 minutes after the onset of tDCS. Brain stimulation is conducted in a room next to the scanner and structural and resting-state (rs-fMRI) scans are conducted immediately before and after both active and sham tDCS (Fig 2). To keep the time interval stable, we start the post-stimulation rs-fMRI 5 minutes after the end of stimulation to move the subject on the scanner bad and prepare it.

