### 2.3 Participants and recruitment

We aim to recruit 48 participants from specialized clinics affiliated with Razi Psychiatric Hospital in Shahre-Rey, Iran, using flyer advertising and referrals from their treating psychiatrists. The exclusion of smokers is not feasible because a significant proportion of patients with SCZ are smokers. The expected population is SCZ patients with cognitive impairment (see inclusion criteria) who are not in a severe stage. Below are the inclusion and exclusion criteria:

Inclusion Criteria:

To be eligible for participation, individuals must meet the following criteria

Age: Men or women aged 18–55 years.Diagnosis of schizophrenia or schizoaffective disorder according to DSM-5 with the native language version of the DSM-5 Clinician-Rated Dimensions of Psychosis Symptom Severity [33] and the native language version of the Positive and Negative Syndrome Scale [31] conducted by two skilled licensed psychiatrists. Patients with disorganized or negative motor behaviors will not be included.Cognitive Impairment: Should exhibit significant cognitive impairment, defined as performance of at least one standard deviation below the norm on working memory/executive functioning tasks measured by a native language version [27] of the Montreal Cognitive Assessment [34].Feasibility: Must be suitable for tDCS interventions following safety guidelines.Treatment with stable doses of antipsychotics and all CNS-activating medications (4–6 weeks before the experiment). For the purpose of this study, stability is defined as a change of not more than 50% in the antipsychotic dose.Right-HandednessInformed Consent: Written and witnessed informed consent (the informed consent is provided by independent research assistants and not the treating psychiatrist to avoid coercive treatment)Participants must read and write in Persian at a level sufficient to understand and complete study-related procedures

Exclusion Criteria:

Participants will be excluded from the study if they meet any of the following criteria.

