### 2.5 Sample size estimation

The sample size is determined a priori through power analyses via G*Power 3.1 [35], indicating that a minimum of 42 subjects is required to achieve 95% power at a significance level of 0.05 for the primary statistical test of a mixed-model ANOVA design, with two groups, 3 measurements of working memory performance (baseline, during stimulation and 24 hours after stimulation), given a medium effect size (f = 0.25, equivalent to η^p2^ = 0.10 which is used in ANOVA models). This effect size is recommended in NIBS studies [36]. To account for a potential dropout rate during the study, we propose including an additional 3 participants in each group (i.e., 6), totaling 48, which is more than the majority of published studies in terms of sample size and retention rate [37, 38].

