#### 2.10.3 Exploratory outcomes

We will perform exploratory analyses to investigate the correlations between changes in physiology and changes in cognitive performance before and after tDCS. This approach allows us to assess the intricate relationship between brain function and behavior. Furthermore, our objective is to identify potential predictors of variations in working memory task performance and individual responses to the intervention, taking into account a range of clinical and biological measures. In addition, we will incorporate the induced electric field (E-field) in the prefrontal area for each participant. This E-field is determined through an analysis of the computational finite-element model with simNIBS software and is considered as a potential predictor of how the brain responds to tDCS.

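### Sleep pressure is checked on the stimulation day as a strong influence on performance, but the stated n-back model does not use it, at some cost in precision

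*Protocol article*

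**What the plan says.** All references are to the protocol article.

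- **Section 2.1 (Trial design, text after Fig 1).** At the start of the intervention session, "participants are first checked for sleep pressure as it greatly impacts cortical excitability, tDCS-induced plasticity and cognitive performance". The article names no instrument or threshold and does not say what follows from the check.
- **Section 2.1, same paragraph.** "At least one week prior to participating in the intervention session (tDCS/fMRI), a baseline assessment of working memory is conducted using the n-back test". No sleep check is described for that visit.
- **Section 2.12 (Statistical methods).** The n-back indices (d-prime, reaction time, accuracy) go into a mixed ANOVA "with time (before and after tDCS) as the within-subject factor and group (active tDCS and sham tDCS) as the between-group factor and their interaction". Assumption tests and a sphericity correction are listed. No covariate is.
- **Section 2.10.3 (Exploratory outcomes).** Predictors of working memory performance and of individual response will be sought, "taking into account a range of clinical and biological measures". Sleep pressure is neither named nor excluded.
- **Section 2.5 (Sample size).** "a minimum of 42 subjects is required to achieve 95% power at a significance level of 0.05", for a design "with two groups, 3 measurements of working memory performance (baseline, during stimulation and 24 hours after stimulation", at f = 0.25. Six further participants bring the total to 48, or 24 per arm.

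**The concern.** The plan itself calls sleep pressure a strong influence on cognitive performance, a primary outcome domain, and checks it before stimulation starts. A strongly prognostic variable measured before treatment is a natural covariate, yet the stated efficacy model leaves it out.

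The timing of the n-back matters here. The before-versus-during contrast compares two days at least a week apart. Subtracting or adjusting for baseline removes stable differences in ability. It does not remove how sleepy a person happens to be on the stimulation day. That variation stays in the error term of the group-by-time test. With 24 per arm, a chance difference in sleepiness between the arms also goes uncorrected in the single estimate the trial will produce.

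What is at stake is the width of the confidence interval for the n-back effect and the power of its test.

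**Working it through.** **Inputs from the article.** Two arms; 42 participants as the minimum and 48 planned (24 per arm); alpha 0.05; f = 0.25; three measurements in section 2.5 and a two-level time factor in section 2.12.

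**Assumed, because the article does not give them.**
- Correlation among repeated measures 0.5 and sphericity 1.
- Partial correlation r of session-day sleep pressure with the session n-back score, given baseline: 0.1 to 0.5.

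**Step 1: the plan's own figure.** For the group-by-time interaction with m measurements:

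λ = f² × N × m / (1 − ρ), df1 = m − 1, df2 = (N − 2)(m − 1)

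With m = 3 and N = 42, λ = 0.0625 × 42 × 3 / 0.5 = 15.75 on 2 and 80 df, and power is 0.946. The stated 42 for 95% is reproduced within rounding; the smallest even N that reaches 0.95 is 44. With the two-level time factor, λ = 0.0625 × 42 × 2 / 0.5 = 10.5 on 1 and 40 df, and power is 0.885.

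**Step 2: what the covariate buys, two-arm comparison.** Adjusting for a covariate with partial correlation r multiplies the residual variance by 1 − r². This is worth a sample 1/(1 − r²) times as large. Take 24 per arm and a two-sided test. The reference effect is set to give 80% power without the covariate (d = 0.826, 46 df). With the covariate there are 45 df, and the noncentrality is d × √12 / √(1 − r²) = 2.862 / √(1 − r²).

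| r (assumed) | Residual variance | Equivalent extra participants | Power, from 80% | Power, from 95% |
|---|---|---|---|---|
| 0.1 | 0.99 | 1% | 80.4% | 95.2% |
| 0.2 | 0.96 | 4% | 81.5% | 95.7% |
| 0.3 | 0.91 | 10% | 83.5% | 96.5% |
| 0.4 | 0.84 | 19% | 86.3% | 97.6% |
| 0.5 | 0.75 | 33% | 89.9% | 98.6% |

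The last column repeats the calculation with d = 1.063, the effect that has 95% power unadjusted. The gain is about 0.4 to 10 points from 80% and about 0.2 to 3.6 points from 95%. If the covariate explained nothing, the lost degree of freedom would cost about 0.04 of a point (79.96% instead of 80%).

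**Step 3: the same question in the plan's ANOVA.** Divide λ by 1 − R², where R² is the assumed share of residual change variance explained, and remove the covariate's degrees of freedom. At N = 42:

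| R² (assumed) | Three measurements | Two measurements |
|---|---|---|
| 0 | 0.946 | 0.885 |
| 0.05 | 0.956 | 0.900 |
| 0.10 | 0.965 | 0.915 |
| 0.20 | 0.980 | 0.942 |
| 0.30 | 0.991 | 0.965 |

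The gain is about 1 to 4.5 points with three measurements and 1.5 to 8 with two.

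**Step 4: validity.** In 20,000 simulated null trials with 21 per arm, omitting a covariate that explains 0 to 30% of the variance left type I error at 0.050 to 0.052 and the mean group difference at about 0.00 SD.

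**Step 5: how the covariate must enter.** A single sleep score per person, added to the mixed ANOVA only as a main effect, explains differences between people in their average level. The group-by-time test uses within-person error, which such a term leaves untouched. To sharpen that test the score must act on change. This means a sleep-by-time term, or equivalently in purpose an analysis of the session score adjusted for baseline score and sleep score.

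**The case against.** **Unadjusted analysis of a randomised trial is legitimate, and covariates are often left to an analysis plan.** This stands as far as validity goes, and an analysis plan not shown here may add the term. But section 2.12 states the terms of the efficacy model, so the point concerns a stated choice that could be better.

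**The check may be a gate.** If sleepy participants are rescheduled, the range on the day is already narrowed and the covariate would gain little. The article does not say which it is. A reader might infer that known day-of-test noise certainly remains in the comparison; the text does not establish that.

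**A reader might infer that sleep pressure is used in no analysis at all.** Section 2.10.3 keeps an open list of exploratory predictors that could include it. It is fair to say only that the stated n-back model does not use it. An exploratory predictor search would not adjust the primary comparison.

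**A reader might infer that sleep is not assessed at baseline.** The schedule figures (Figs 1 and 2) are not shown and the article is condensed, so absence from the text does not prove this.

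**A reader might extend the argument to connectivity.** Both resting-state scans are taken on the session day, just before and after stimulation, so the change between them already removes most of a shared sleep effect. The week-long gap applies only to the n-back.

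**A reader might extend it to smoking**, since section 2.3 says that "The exclusion of smokers is not feasible because a significant proportion of patients with SCZ are smokers". Smoking is broadly a stable trait, and a constant effect on score level cancels in the group-by-time contrast. The article gives no ground for thinking that it alters the change over time.

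**The size is assumed.** This stands. No correlation is given in the article, and at r = 0.1 or 0.2 the gain is under 2 points.

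**Conclusion.** The point holds as a matter of efficiency. The plan names sleep pressure as a strong influence on cognitive performance and checks it before stimulation, and the stated n-back model leaves it out. Baseline n-back, at least a week earlier, cannot stand in for it.

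The consequence is some lost precision in the n-back comparison. Inferring bias or an inflated type I error would go too far: randomisation protects the contrast, and the simulations show neither.

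The size cannot be derived from the document. It runs from about 0.4 to 10 power points from an 80% starting point, and about 0.2 to 3.6 from 95%, for assumed partial correlations of 0.1 to 0.5. These figures rest on 24 analysed per arm, a linear effect of sleep pressure that is the same in both arms, and a check that yields a usable score with some spread. No figure in the protocol becomes wrong.

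**What to change.** 1. Record the existing session-day check as a score, and state the instrument and what, if anything, follows from the result.
2. Pre-specify that score as a covariate for the n-back comparison, so that it acts on the group-by-time contrast. Either analyse the session score by group with baseline score and sleep score as covariates, or add a sleep-by-time term to the mixed ANOVA. A main effect alone would not help.
3. Optionally, repeat the same short rating at the baseline and 24-hour n-back. The session-day score describes the stimulation day, so it is of less use for the 24-hour measurement.

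The cost is one degree of freedom of about 46 and the recording of a check that is already made. If the check also acts as a gate, the score will vary little and the gain will be small, but adjustment would do no harm. Because the score precedes stimulation, adjusting for it cannot remove part of a treatment effect. Section 2.1 says that recruitment is under way, so the change should be made soon and fixed before unblinding. Where no score was recorded for participants already seen, it will have to be treated as missing.
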